#### **Adverse Reaction (AR)**

Adverse reaction is defined as a response to a medical product which is noxious and unintended. An AR is any AE judged as having a reasonable suspected causal relationship to a medicinal product.

#### **Causal relationship**

The assessment of the causal relationship between an AE and the use of the study product is a clinical decision by the investigator based on all available information at the time of the completion of the CRF. The assessment is based on the question whether there was a "reasonable causal relationship" to the study product in question. Possible answers are "yes" or "no".

An assessment of "no" would include:

- 472 1. The existence of a clear alternative explanation
- 473 2. Non-plausibility
- 474 An assessment of "yes" indicates that there is a reasonable suspicion that the AE is associated
- 475 with the use of the study product. Factors to be considered in assessing the relationship of the AE
- 476 to study product include:
- 477 3. The temporal sequence from the use of product: The event should occur after the product is given.
- 478 The length of time from product exposure to event should be evaluated in the clinical context of
- 479 the event.
- 480 4. Recovery on product discontinuation (de-challenge), recurrence on product re-introduction (re-
- 481 challenge): Subject's response after de-challenge or subject's response after re-challenge should
- 482 be considered in the view of the usual clinical course of the event in question.
- 483 5. Underlying, concomitant, intercurrent diseases: Each event should be evaluated in the context of
- 484 the natural history and course of the disease being treated and any other disease the subject may
- 485 have.
- 486 6. Concomitant medication or treatment: The other products the subject is taking or the treatment the
- 487 subject receives should be examined to determine whether any of them may be suspected to cause
- 488 the event in question.
- 489 7. Spontaneous case reports from consumers or health care professionals are generally considered to
- 490 be adverse reactions, since the act of reporting a case is assumed to imply a judgment of possible
- 491 causality on the part of the reporter, unless there is a clear statement from the reporter that a
- 492 causal relationship can be excluded.

493 **Serious adverse event/serious adverse reaction**

494 An adverse event (AE) or adverse reaction (AR) is serious if it:

- 495 2. results in death,
- 496 3. is life-threatening
- 497 4. requires inpatient hospitalization or prolongation of existing hospitalization.

498 A hospitalization or prolongation of hospitalization will not be regarded as a serious adverse event  
499 (SAE) if at least one of the following exceptions is met: (1) the admission results in a hospital stay  
500 of less than 12 hours; (2) the admission is pre-planned (i.e. elective or scheduled surgery arranged  
501 prior to the start of the study); (3) the admission is not associated with an AE (e.g. social  
502 hospitalization for purpose of respite car.

503 However, it should be noted that invasive treatment during any hospitalization may fulfill the  
504 criterion of 'medically important' and as such may be reportable as an SAE dependent on the  
505 clinical judgment. In addition, where local regulatory authorities specifically require a more  
506 stringent definition, the local regulation takes precedence;

- 507 5. results in persistent or significant disability or incapacity
- 508 6. is a congenital anomaly, birth defect or fetal mental impairment
- 509 7. is medically significant:
- 510 ○ Medical and scientific judgment should be exercised in deciding whether an AE/AR may be
- 511 considered serious (due to an important medical event) because it jeopardizes the health of the

patient or may require intervention to prevent another serious condition (death, a life-threatening condition, hospitalization or persistent or significant disability).

○ Examples of such events are:

- invasive treatment during any hospitalization, in an emergency room or at home for allergic bronchospasm
- blood dyscrasia or convulsions that do not require hospitalization
- development of any drug dependency or abuse
- lack of drug effect if the product was used for the treatment of acute life-threatening diseases (apply medical judgment) or reports of any transmission of an infectious agent via a product

### **Investigational medical product**

1. Medical product being assessed for safety or performance in a clinical investigation
2. NOTE: This includes medical products already on the market that are being evaluated for new intended uses, new populations, new materials or design changes.

### **Collection**

After enrollment into the study, all non-serious adverse events (AE) must be documented on the AE Report Form or in the CRF/EDC system and forwarded to the sponsor within 7 calendar days of awareness. All serious AEs (SAE) must be documented and forwarded immediately (within one business day of awareness). For each AE, the investigator or a delegate must assess and document the seriousness, duration, relationship to product, action taken and outcome of the event.

If a pregnancy occurs during the study, although it is not a serious adverse event itself, it should be documented and forwarded to the sponsor within the same time limits as a serious adverse event. The result of a pregnancy will be followed-up according to applicable SOPs. Any data on abnormal findings concerning either the mother or the baby will be collected as adverse events.

All drug related events must be documented on the product related CRF form or in the CRF / EDC system and also on the PTC form(s). Incidents must be forwarded to the study initiator and funder within 24 hours (immediately) and other events must be forwarded within 7 calendar days of awareness. Products suspected of defects should be retained for recycling and returned to the sponsor for further inspection and verification

The documentation of any AE/SAE/drug related events ends with the completion of the observation period of the patient. However, any AE/SAE - regardless of the relationship and the seriousness - occurring within  $30 \pm 7$  days after the last use of MMF within the study period has to be documented and forwarded to the sponsor within the given timelines, even if this period goes beyond the end of observation.

As long as the patient has not used any MMF within the frame of the study AEs /SAEs do not need to be documented as such in this observational study. However, they are part of the patient's medical history.

For any serious product-related AE occurring after study end, the standard procedures that are in place for spontaneous reporting has to be followed.

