**Safety endpoints**

1. Including all adverse events (AEs), serious adverse events (SAEs), study drug-related SAEs, AEs leading to study withdrawal, and AEs related to the study drug occurred during the study period will be recorded.
1. SAEs were defined as death, life-threatening conditions, requiring inpatient hospitalization or prolongation of existing hospitalization.
2. AEs with special concern were defined as drug-related AE listed in the drug information provided by the pharmaceutical manufacture of MMF, including leukopenia or leukocytosis, anemia, sepsis, gastrointestinal symptoms (diarrhea, stomachache, vomiting, anepithymia), certain types of repeated infections (pneumonia, influenza syndrome, urinary tract infection, herpes zoster, etc.), hepatic dysfunction or transaminase elevation, malignancy.

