### Analysis sets

1. ITTs (Intention-to-test set): All enrolled subjects who sign the informed consent and undergo randomization. ITTs will be used for all efficacy analyses
2. SS (Safety set): All enrolled patients who have used the study drug. The SS set will serve as the primary analysis population for all safety outcomes.

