#### **Serious AEs**

Any SAE or pregnancy entered into the CRF/EDC system will be forwarded immediately by the EDC system (or alternatively the study staff manually within one business day of awareness) to the pharmacovigilance country head being responsible for SAE processing. The outcome of all reported SAEs (resolution, death etc.) will be followed up and documented. Where required, investigators might be contacted directly by the pharmacovigilance country head in charge to provide further information.

For SAEs that occurred while administering non-MMF the investigator has to account for and comply with the reporting system of the product's Marketing Authorization Holder within the frame of local laws and regulations as well as other locally applicable laws and regulations.

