## 3.7. Safety Endpoints

### 3.7.1. Adverse Events

#### (1) AEs/SAEs

AEs/SAEs occurred during the study period from the first application of MMF to 30±7 days after the last use of MMF will be analyzed and summarized.

**Adverse event (AE):** Any untoward medical occurrence in a patient with the use of a medical product and which does not necessarily have to have a causal relationship (association) with this product. An AE can therefore be any unfavorable and unintended sign (including an abnormal laboratory finding), symptom, or disease temporally associated with the use of the study device, whether or not related to the product.

**Adverse Reaction (AR):** is defined as a response to the study device which is noxious and unintended. An AR is any AE judged as having a reasonable suspected causal relationship to the study device. The assessment of the causal relationship between an AE and the use of the study device is a clinical decision by the investigator based on all available information at the time of the completion of the CRF. The assessment is based on the question whether there was a "reasonable causal relationship" to the study device in question. Possible answers are "yes" or "no".

**Serious adverse event/serious adverse reaction:** an adverse event (AE) or adverse reaction (AR) is serious if it:

- results in death,
- is life-threatening
- requires inpatient hospitalization or prolongation of existing hospitalization.
- results in persistent or significant disability or incapacity
- is a congenital anomaly, birth defect or fetal mental impairment
- is medically significant: Medical and scientific judgment should be exercised in deciding whether an AE/AR may be considered serious (due to an important medical event) because it jeopardizes the health of the patient or may require intervention to prevent another serious condition (death, a life-threatening condition, hospitalization or persistent or significant disability).

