### **5.2. Safety Set (SS)**

SS is a subset of ITT. It consists of ITT participants excluding the ones without taking any study medication or having no record of follow up after randomization. SS will be used for the safety analysis.

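### Protocol section 9 contradicts itself, section 7.7 and Table 1 on whether adverse events are recorded in patients who have not used MMF; if its exemption is followed, the safety comparison between arms is biased

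*Combined protocol and SAP*

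**What the plan says.** The recording rules in the protocol point in two directions.

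- **Exempting patients without MMF.** Section 9, Collection: "As long as the patient has not used any MMF within the frame of the study AEs /SAEs do not need to be documented". The same sentence calls the trial an observational study, and the next one treats such events as medical history.
- **Requiring events in everyone.** The same subsection opens with "After enrollment into the study, all non-serious adverse events (AE) must be documented on the AE Report Form" and "All serious AEs (SAE) must be documented and forwarded immediately", with no condition on arm or exposure. Section 7.7, Safety endpoints, lists all AEs and SAEs first and ends "AEs related to the study drug occurred during the study period will be recorded". Table 1, in both protocol and SAP, marks AEs/SAEs at Visits 3 to 28 without distinguishing arms. That starts before randomisation (Visit 5) and before the first dispensing (Visit 6).
- **Other products.** Section 9, Serious AEs: "For SAEs that occurred while administering non-MMF the investigator has to account for and comply with the reporting system" of that product's authorisation holder. The subsection on non-serious ARs has a parallel rule.

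The analysis rules are also tied to MMF. SAP 3.7.1 analyses "AEs/SAEs occurred during the study period from the first application of MMF" until 30±7 days after the last use. Protocol 7.12 defines "SS (Safety set): All enrolled patients who have used the study drug". SAP 5.2 says of its safety set: "It consists of ITT participants excluding the ones without taking any study medication or having no record of follow up after randomization", and the only study drug listed in SAP 3.2 is MMF. SAP 6.4 nevertheless plans Fisher's exact test on the proportions of patients with at least one event, and SAP 4.4 sets a two-sided 0.05 level for safety analyses.

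**The concern.** Supportive-care patients are never assigned MMF, so a site that applies the exemption as written has no duty to document their events: at most 84 × 3 = 252 patient-years, before losses. The same wording exempts MMF patients between randomisation (week 0) and first dispensing (Visit 6, week 4). Treatment is open-label, so staff know which patients the sentence covers. Even patchy use of it would make recording depend on arm.

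A difference in AE proportions could then reflect documentation rather than drug effect. Analysis cannot restore events that were never written down. This matters for an immunosuppressant, whose harms are half of the benefit-risk question.

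**Working it through.** **1. Can the rules all be followed?** For a supportive-care patient with an SAE at week 60, the opening of Collection, section 7.7 and Table 1 require documentation, while the later sentence in Collection waives it. No single practice satisfies every passage.

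**2. Arm size.** The plan gives no AE risk and no documentation rate, so the only usable planned figure is the number per arm. With 36% versus 16%, 80% power and two-sided 0.05 (Protocol 7.4):

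n = [1.96·√(2·0.26·0.74) + 0.842·√(0.36·0.64 + 0.16·0.84)]² / 0.20² ≈ 74.3, so 75 per group.

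The plan states 76 (power at 76: 80.9%). For the 10% loss, 76 × 1.1 = 83.6 gives the stated 84, and 76/0.9 gives 85. The figure reproduces. The sample size is not at issue; 84 per arm only illustrates the effect.

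**3. Effect of unequal documentation.** Let p be the true risk of at least one event, equal in both arms, and c the probability that a control patient with an event is documented. The MMF arm is assumed fully documented. Recorded counts are then X ~ Bin(84, p) on MMF and Y ~ Bin(84, c·p) in controls, and the apparent relative risk is 1/c. Summing the exact probability of all (X, Y) pairs with two-sided Fisher p<0.05 gives:

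| True risk p | c = 1 | c = 0.75 | c = 0.5 | c = 0.25 | c = 0 |
|---|---|---|---|---|---|
| 5% | 1.7% | 2.3% | 4.8% | 10.8% | 24.3% |
| 10% | 2.9% | 5.3% | 15.4% | 40.0% | 85.7% |
| 20% | 3.1% | 9.6% | 36.7% | 81.7% | about 100% |
| 30% | 3.4% | 15.4% | 58.4% | 96.0% | about 100% |

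With equal documentation, about half of the rejections point to MMF harm (0.9% to 1.7% of trials over these risks). At c = 0.5 or below, practically all do. If no control patient has a recorded event, 6 MMF patients with one already give p<0.05.

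**4. A bias in the other direction.** Suppose instead that controls are fully recorded and counted for 156 weeks, while MMF patients are counted only to 30 days after the last dose. Assume the last dose falls at week 78, counting starts at week 0 and the hazard is constant.

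- Fraction of follow-up counted on MMF: (78 + 30/7)/156 = 82.3/156 = 0.527.
- A true 30% risk appears on MMF as 1 − 0.70^0.527 = 17.1%. Fisher then favours MMF in 44% of trials.
- A true 20% risk appears as 11.1%, and Fisher favours MMF in 28% of trials.

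Maintenance is for a minimum of 6 months, so longer use would shrink this effect.

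**5. A third outcome.** If both safety-set definitions are read literally, supportive-care patients fall out of the set and no comparison between arms takes place.

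**The case against.** A reader might infer that control events need never be recorded and that equal risks will therefore look like MMF harm. The documents do not support this. The opposite duty is written in the same subsection, in section 7.7 and in Table 1, so practice depends on which text a site followed. The direction is not fixed either, as steps 4 and 5 show.

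A reader might also infer that SAEs under other products go to the authorisation holder instead of into the trial record. The text imposes that reporting but does not say it replaces trial reporting, and the same subsection forwards any SAE entered in the EDC.

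Other points on the plan's side have weight:

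- The exemption can be read as a pre-first-dose rule, especially with the following sentence about medical history. That may be the intent, but the literal wording still reaches patients who never receive MMF.
- At low risks or mild under-recording the distortion is small: about 5% at a 5% risk with half documentation, and 2% at a 5% risk with three-quarters documentation.
- SAP 6.4 says safety analyses involve no formal hypothesis testing, although it then specifies Fisher tests. No stated decision hangs on p<0.05.
- Some safety information does not depend on AE forms. Table 1 schedules haematology and chemistry at every visit from Visit 5 in both arms, and SAP 6.4.2 compares laboratory variables with a mixed model. ESRD and kidney or cardiovascular death are adjudicated blind.

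These points limit the size and reach of the problem. They do not remove the contradiction, and clinical events such as infections and gastrointestinal symptoms still rest largely on AE documentation.

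**Conclusion.** The contradiction is certain and must be resolved. The bias is conditional. If the exemption is followed, control events are under-recorded and the Fisher comparison leans toward apparent MMF harm: at half documentation about 5%, 15%, 37% and 58% of trials reach p<0.05 at true risks of 5%, 10%, 20% and 30%, and with none documented 24%, 86%, about 100% and about 100%. With equal documentation the figures are 1.7% to 3.4%. These results rest on 84 per arm, equal true risks, full documentation on MMF, and assumed values for risk and documentation. A window applied only to the MMF arm could produce the opposite bias. The documents do not show which rule sites used, so neither the presence nor the direction of a bias can be asserted.

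**What to change.** Recording, window and safety set have to be changed together, because correcting one leaves the others broken.

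1. **Protocol 9, Collection.** Delete the sentence that exempts patients without MMF, and reconcile the subsection with 7.7 and Table 1. Suggested text: *AEs and SAEs are documented in the EDC and forwarded on the same timelines in both arms from randomisation to the end of each patient's observation, whether or not MMF has been taken. Run-in events are recorded as in Table 1.*
2. **Protocol 9, Non-serious ARs and Serious AEs.** State that reporting to another product's authorisation holder is in addition to trial reporting.
3. **SAP 3.7.1.** Define both the start and the end of the analysis window identically for both arms. List separately any further events captured only because of the post-MMF follow-up.
4. **Protocol 7.12 and SAP 5.2.** Define the safety set so that supportive-care patients are included.

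Before or during conduct, the cost is amendment wording, matching SAP text and site retraining. The visits and the AE/SAE row already exist for all patients.

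SAP section 3 describes recruitment and follow-up in the past tense. If conduct is complete, rewording cannot recover missing events. The report should then state which rule sites followed, control medical records should be checked where possible, and the AE comparison should be described as limited by possible differential documentation.

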### **Management and reporting**

#### **Non-serious AEs**

The outcome of all reported AEs will be followed up and documented. Where required, investigators might be contacted directly by the responsible study staff to provide further information.

#### **Non-serious ARs**

For non-serious ARs occurring under non-MMF the investigator has to account for and comply with the reporting system of the product's Marketing Authorization Holder within the frame of local laws and regulations as well as other locally applicable laws and regulations.

#### **Serious AEs**

Any SAE or pregnancy entered into the CRF/EDC system will be forwarded immediately by the EDC system (or alternatively the study staff manually within one business day of awareness) to the pharmacovigilance country head being responsible for SAE processing. The outcome of all reported SAEs (resolution, death etc.) will be followed up and documented. Where required, investigators might be contacted directly by the pharmacovigilance country head in charge to provide further information.

For SAEs that occurred while administering non-MMF the investigator has to account for and comply with the reporting system of the product's Marketing Authorization Holder within the frame of local laws and regulations as well as other locally applicable laws and regulations.

#### **Incidents**

All drug-related events will be forwarded to the pharmacovigilance staff being responsible for product event processing. Product technical complaints not related to an AE/SAE will be forwarded to the relevant quality department. The outcome of all reported incidents (resolution, death etc.) will be followed up and documented. Where required, investigators might be contacted directly by the pharmacovigilance staff in charge to provide further information.

For any MMF related events occurring after study end, the standard procedures that are in place for spontaneous reporting has to be followed.

According to relevant local regulations, AE/SAE/medical product events related to the use of medical product and product defects that may cause serious adverse events should be submitted by the medical product prescription-provider institution to the relevant regulatory authority within the prescribed time limit.

#### **Evaluation**

Whenever new important safety information is received, e.g. case reports from an investigator, the reports are processed and entered into the pharmacovigilance safety database. These reports will be reviewed on a regular basis (for information on collection, management and reporting of case reports, refer to 0 and 0). If a potential safety signal is suspected, an investigation of the suspected potential signal will be performed according to internal standard operating procedures, for further evaluation within the context of benefit risk.

## Abbreviations

|       |                                          |
|-------|------------------------------------------|
| AE    | Adverse Event                            |
| ANOVA | Analysis of Variance                     |
| AR    | Adverse Reaction                         |
| BMI   | Body Mass Index                          |
| DBP   | Diastolic Blood Pressure                 |
| eGFR  | Estimated Glomerular Filtration Rate     |
| ESRD  | End Stage Renal Disease                  |
| HPF   | High Power Field                         |
| HR    | Hazard Ratio                             |
| ID    | Identification                           |
| IgA   | Immunoglobulin A                         |
| ITTs  | Intention-to-Test Set                    |
| KDIGO | Kidney Disease Improving Global Outcomes |
| LOCF  | Last Observation Carry Forward           |
| MAP   | Mean Arterial Pressure                   |
| MMF   | Mycophenolate Mofetil                    |
| PI    | Principal Investigator                   |
| RAS   | Renin-Angiotensin System                 |
| RBCs  | Red Blood Cells                          |
| SAE   | Serious Adverse Event                    |
| SAP   | Statistical Analysis Plan                |
| SBP   | Systolic Blood Pressure                  |
| SD    | Standard Deviation                       |
| SOP   | Standard Operating Procedure             |
| SS    | Safety Set                               |
| TLF   | Tables, Listings and Figures             |
| UPE   | Urine Protein Excretion                  |
| WBCs  | White Blood Cells                        |

